### Adverse event collection procedure during the trial

The adverse events will be truthfully reported and handled and recorded in a timely manner. Follow-ups will be conducted to find out the reasons and to ensure the health, safety, and rights of the subjects. Serious adverse events will be reported within 24 h to the main researchers, the Clinical Trial Office of Xuhui Central Hospital, and the Ethics Committee of Shanghai Xuhui Central Hospital and the subjects will receive appropriate counseling.

### Trial setting

The study will be carried out in the Department of Rehabilitation Shanghai Xuhui Central Hospital. All patients will receive comprehensive rehabilitation provided by physiotherapists, including exercise therapy, occupational therapy, daily life ability training, and traditional physical therapy.

### Inclusion criteria

Subjects will have to satisfy all of the following criteria to be included in the study: 1) meet the diagnostic criteria of cerebral infarction or hemorrhage; 2) meet the traditional Chinese medicine (TCM) diagnostic criteria of apoplexy; 3) had their first brain stroke with dysarthria; 4) were diagnosed with a FDA score < 27 and dysarthria combined with a ≥ b scale of pulmonary function during speech according to the FDA criteria (revised by the Rehabilitation Center of Hebei Provincial People’s Hospital; 5) are in a phase 2 weeks to 6 months after stroke; 6) have enough physical strength to complete 40-min speech training; 7) have a sitting balance ranking ≥ 3; 8) have at least normal unilateral upper-limb movement function or Brunnstrom stage of ≥ 4; 9) have normal and stable vital signs; and 10) have a willingness and ability to provide written informed consent.

### Exclusion criteria

Subjects will not be enrolled if they meet any of the following exclusion criteria: 1) unconsciousness and severe cognitive impairment; 2) combined with aphasia; 3) incapable of completing 40-min speech breathing training; 4) have complications such as acute disease in major organs of the heart, brain, and kidney; 5) serious psychological disorders.

### Study population and recruitment

A total of 100 patients aged from 40 to 80 years who are diagnosed with stroke in the Department of Rehabilitation in Shanghai Xuhui Central Hospital from Dec 2016 to Dec 2019 will be recruited into the study.

The recruitment procedure of patients will involve four steps: 1) the patient’s attending physician will need to be familiar with the criteria for inclusion and exclusion of a patient into the study, screen potential subjects, and contact the primary researcher. 2) The researcher will introduce the trial to potential subjects and discuss the objectives with them based on the test requirements and schedule, and potential participants will be asked for their opinions. 3) According to the inclusion and exclusion criteria, the participants will be judged as eligible or ineligible for inclusion. 4) Participants need to sign a consent form to participate in the trial.

### Randomization

Subjects will be randomized 1:1 using simple randomization via random numbers generated in Excel. To make sure that the risk of bias remains low, patients will be registered in the database by means of a patient ID code so that assessors are blinded during the analysis. Only the primary investigator will have knowledge about the allocation. The outcome assessors and care providers will be different doctors. A special evaluation team will be set up and two senior speech therapists will undertake the assessment work. The outcome assessors and care providers will not exchange information during the implementation of the experiments, and the outcome assessors shall not ask the subject for the intervention to ensure accuracy of the assessment.

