### Sample-size calculation

We anticipate that the effective rate of speech breathing-specific curative effect assessed by modified FDA will be 70 and 40% for the study and control groups, respectively. Under such an assumption, 41 participants per group (on a 1:1 ratio) will be needed to show a significant difference at a *P* value < 0.05 with a test power of 80%. Anticipating losses of 18% in follow-ups, we will establish a target sample size of 100 participants (50 participants in each group).

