### Statistical analysis

In the study, the main indicator, “speech breathing level according to modified Frenchay Dysarthria Assessment (FDA)”, will be ranked data. The statistical method will be as follows. (1) The main indicator will be compared between baseline and follow-up time with a signed rank test. The score change will be compared between groups using a rank-sum test. Unless indicated otherwise, hypothesis testing will use a two-sided test with *P* = 0.05 as the statistical cutoff point. (2) The influence of rehabilitation intervention time, stroke classification, age, and gender on the efficacy of the intervention method and the relative size of the efficacy will be estimated using a stepwise logistic regression model. (3) The overall efficacy evaluation will be the effective rate. The formula will be: Effective rate = (Excellent + Effective)/Total number of cases × 100%. A chi-squared test will be used to compare any differences in efficacy between the two groups.

The secondary outcomes will be analyzed using a repeated measure covariance analysis with the outcome baseline adjusted for as a covariate. We will test whether there is a statistically significant difference between the groups using a parameter representing treatment allocation. The ‘loudness level’ outcome is ranked data and will be analyzed in a similar way to the primary outcome.

The per-protocol (PP) population will include the randomized patients of the intention to treat (ITT) population but exclude those for whom the inclusion or exclusion criteria were not met and those who did not receive the actual treatments to which the patients were randomly allocated [18]. If the statistical results of the ITT and PP population data are the same, the results will be deemed to be reliable; if they are contrary, we intend to adopt the results of the ITT population. The method of processing missing data will be the last observation carried forward (LOCF). This refers to assigning the last observed value of the end point indicator to the subsequent missing evaluation point; that is, the last observation response will be considered to be the study end point.

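### Simple randomization guarantees neither equal arms nor balance on starting grade or time since stroke, and the primary between-group tests adjust for neither factor

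*Protocol article*

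**What the plan says.** Protocol article, Randomization: "Subjects will be randomized 1:1 using simple randomization via random numbers generated in Excel". No blocks, strata or minimisation are named. The Sample-size calculation section says "we will establish a target sample size of 100 participants (50 participants in each group", and the abstract also gives 50 per group.

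Under Inclusion criteria, patients may enter at any speech-breathing grade from b downwards, and between 2 weeks and 6 months after stroke. The Primary outcome section scores grades a to e as 1 to 5. A fall of two or more grades, or reaching grade a, is CR; a fall of one grade is PR; anything else is NR.

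Under Statistical analysis, the between-group tests of the primary outcome are a rank-sum test on score change and a chi-squared test on the effective rate. No covariate is named for either. A stepwise logistic model looks at rehabilitation intervention time, stroke classification, age and gender. The secondary outcomes, by contrast, are adjusted for their baseline value.

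**The concern.** The amount a patient can change depends on where that patient starts. If one arm happens to receive more patients at grade d or e, it has more room for large score changes, and the unadjusted rank-sum test cannot separate this from a treatment effect in that particular sample. The response categories also depend on the start: one step from grade b reaches grade a and is CR, while one step from c, d or e is PR. Time since stroke varies widely at entry, and neither the allocation nor the primary tests take account of it.

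At stake are the precision of the primary comparison and how readily its result can be interpreted if the baseline table shows a difference. A smaller matter is that 50 per group is written as though it were fixed, which simple randomization does not ensure.

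**Working it through.** **1. The plan's own sample size.** Inputs from the Sample-size calculation section: effective rates that "will be 70 and 40% for the study and control groups, respectively", "41 participants per group (on a 1:1 ratio) will be needed", "with a test power of 80"%, and "Anticipating losses of 18% in follow-ups". From Statistical analysis: "hypothesis testing will use a two-sided test with *P* = 0.05 as the statistical cutoff point".

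n = [1.960 × √(2 × 0.55 × 0.45) + 0.842 × √(0.7 × 0.3 + 0.4 × 0.6)]² / 0.30² = 41.97, so 42 per group. The stated 41 is within one patient of this, and power at 41 per group is 79.0%. Allowing for loss, 41 / (1 − 0.18) = 50. The plan's figures are reproduced closely enough.

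**2. Arm sizes.** Under simple 1:1 randomization of 100 patients, the size of one arm is Binomial(100, 0.5).

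| Split | Probability |
|---|---|
| exactly 50:50 | 8.0% |
| 55:45 or more unequal | 36.8% |
| 60:40 or more unequal | 5.7% |

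**3. Power cost of unequal arms** (normal approximation, 70% vs 40%).

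| Evaluable | Balanced | Average under simple randomization | Unequal example |
|---|---|---|---|
| 100 | 86.6% | 86.2% | 85.1–85.4% at 40:60 |
| 82 | 79.0% | 78.6% | 77.3–77.7% at 33:49 |

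The average loss is about 0.4 points in both rows.

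**4. Chance imbalance of a binary baseline factor.** The article gives no baseline distribution, so the prevalence p is an assumption. With 50 per arm, the standard deviation of the difference in proportions is √(2p(1 − p)/50).

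| Assumed p | SD of difference | P(≥10 points) | P(≥15 points) | P(≥20 points) |
|---|---|---|---|---|
| 20% | 8.0 points | 21% | 6% | 1.2% |
| 30% | 9.2 points | 28% | 10% | 2.9% |
| 50% | 10.0 points | 32% | 13% | 4.6% |

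An exact count at p = 50% raises the first figure to 37%: with 50 per arm, a gap of 10 points is 5 patients, and P(difference of 5 or more) is 36.8%. The range is thus about 21% to 37%. For a continuous factor such as time since stroke, the chance that the arm means differ by at least 0.3 SD is 13%.

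**5. How starting grade enters the outcome** (from the scoring and response rules).

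| Start | Largest possible improvement | One step gives |
|---|---|---|
| b | 1 | CR |
| c | 2 | PR |
| d | 3 | PR |
| e | 4 | PR |

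The effect on the score change is mechanical. On the effective rate it is weaker: if effective means CR or PR, one step counts from any grade, and imbalance matters only so far as the chance of improving differs by grade.

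**6. Size of the shift in one trial** (illustration). Suppose the response rate differs by 30 points between factor levels (assumed; range 20 to 40). A 15-point imbalance then moves the group difference by 0.15 × 30 = 4.5 points (3 to 6), and a 20-point imbalance by 0.20 × 30 = 6 points (4 to 8). The planned difference is 70 − 40 = 30 points.

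**The case against.** Simple randomization is a valid method. Chance imbalance is already covered by the test's error rate, so it neither biases the estimate nor inflates the type I error. The article calls its sample size a target, and 50 per group can be read as an expected size. All of this stands.

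The imbalance risk is also not peculiar to simple randomization: the figures in step 4 were obtained with the arms fixed at 50 each. Equal arms alone would not remove it.

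Some cover is planned. The rank-sum test uses change from baseline, and rehabilitation intervention time in the logistic model may mean time since stroke. This cover is partial. A change score does not remove the ceiling set by the starting grade. The logistic model is stepwise, so it may drop its terms, and it does not list baseline grade.

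A reader might infer that the remaining patients should be moved to stratified blocks. The article does not compel that. The trial is single-centre, recruitment was under way at submission, and the limitations section says blinding cannot realistically be achieved. In that setting blocks make assignments easier to guess, and a new list would balance only later patients. A reader might also fear that 50:50 would be restored by hand near the end; nothing in the text describes this.

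**Conclusion.** The point holds as a modest weakness in the primary analysis, not as a fault that invalidates the allocation. Neither the randomization nor the primary between-group tests control for starting grade or time since stroke, although starting grade limits the possible change and the secondary outcomes do receive baseline adjustment.

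The chance of a 10-point imbalance is about 21% to 37%, resting on an assumed prevalence of 20% to 50%. The resulting shift in a single trial is likely to be a few points against a planned 30, resting on the assumed response gap in step 6. The power lost through unequal arms alone is negligible.

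Two stronger readings are not supported. The documents do not rank these two factors as the main determinants of recovery: the case for baseline grade rests on the scoring rule, and that for time since stroke on the wide entry window. Nor do the 8% chance of an exact 50:50 split and the resulting unequal arms threaten the trial's power.

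**What to change.** Pre-specify, for all patients:

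- **Speech-breathing grade:** a rank-sum test stratified by baseline grade (van Elteren), or a proportional-odds model for grade with treatment, baseline grade and time since stroke as fixed terms. Name one of these as primary.
- **Effective rate:** a Cochran-Mantel-Haenszel test stratified by baseline grade, or a logistic model with the same fixed terms, in place of the plain chi-squared test. The terms stay in whatever their P values.
- **Wording:** describe the groups as about 50 each.

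The cost is a short amendment made before the data are analysed. Baseline grade is already collected, and time since stroke has to be known to check eligibility. The allocation list stays as it is. If some grades turn out sparse, a rule for merging adjacent grades should be fixed in advance without reference to treatment.

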### Treatment

The *LQG* (study group) or traditional breathing (control group) training followed by basic articulation training (20 min for each) will be conducted five times per week for 3 weeks in a soundproof, 10 m^2^ room with a background noise of ≤ 30 dBA. Training will be provided by experienced investigators who will ensure that the process is performed in accordance with the protocol. Briefly, a patient will first need to adjust to a straight sitting position, perform relaxing breathing with help from regular upper-limb movement, and be instructed to breathe in smoothly through the nose and exhale slowly through the mouth.

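### As described, allocation concealment is not assured: the lead role that receives and approaches candidates appears to be the role that knows the allocation

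*Protocol article*

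**What the plan says.** Two sections of the protocol article bear on this.

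- **Study population and recruitment** sets out four steps. The attending physician is to "screen potential subjects, and contact the primary researcher". Next, "The researcher will introduce the trial to potential subjects and discuss the objectives with them". Third, "the participants will be judged as eligible or ineligible for inclusion", without naming who makes that decision. Signing of consent comes last.
- **Randomization** gives the method: "Subjects will be randomized 1:1 using simple randomization via random numbers generated in Excel". It then offers its protection against bias: "patients will be registered in the database by means of a patient ID code so that assessors are blinded during the analysis". The next sentence is "Only the primary investigator will have knowledge about the allocation". The rest of the section keeps assessors and care providers apart and forbids them to exchange information.

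Under **Treatment**, "Training will be provided by experienced investigators", so the staff who deliver the two visibly different programmes necessarily know the arm.

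**The concern.** Concealment means that whoever can affect a patient's entry does not know which arm comes next. Read together, the two sections place knowledge of the allocation with what looks like the same lead role through which candidates enter.

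There is room to act on such knowledge. Several entry criteria call for judgement (sufficient physical strength, severity of cognitive impairment, seriousness of psychological disorder), and time since stroke may run from 2 weeks to 6 months. How warmly the trial is presented to a patient is also discretionary.

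The article says under Limitations that single- or double-blind conditions are not realistic, and it appears to concede there that the evaluation is largely subjective. With limited protection after allocation, protection before it carries more weight. The planned chi-squared and rank-sum comparisons adjust for no prognostic factor. The stepwise logistic model considers intervention time, stroke type, age and gender, and cannot remove selection on features that were not recorded, such as motivation.

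**Working it through.** **1. The roles side by side**

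| Step | Role named | Section |
|---|---|---|
| Receives candidates | Primary researcher | Study population and recruitment |
| Introduces and discusses the trial | The researcher | Study population and recruitment |
| Judges eligibility | Not named | Study population and recruitment |
| Knows the allocation | Primary investigator, alone | Randomization |
| Delivers training | Experienced investigators | Treatment |
| Assesses outcome | Two senior speech therapists | Randomization |

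No row separates entry from knowledge of the sequence, and no sentence says whether the primary investigator learns an assignment before or after consent. Unblocked simple randomization cannot be predicted from past assignments. The route to selection is therefore access to the Excel sequence itself, which the text permits and does not rule out.

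**2. What each safeguard does**

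- ID code: masks assessors, after allocation.
- Assessors different from care providers: the same.
- No exchange of information between them: the same.

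All three act against detection bias. None acts before enrolment.

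**3. The plan's own figures (background; not in dispute)**

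Inputs from Sample-size calculation: 70% against 40%, significance 0.05, power 80%, 18% losses. Two-sided testing is from Statistical analysis.

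- Pooled formula: n = [1.96·√(2·0.55·0.45) + 0.842·√(0.70·0.30 + 0.40·0.60)]² / 0.30² = 41.97, so 42 per group.
- Unpooled formula: (1.96 + 0.842)²·0.45 / 0.09 = 39.2, so 40 per group.
- The stated 41 lies between the two. Then 41 / (1 − 0.18) = 50 per group, as stated.

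**4. Illustration of what selective entry could do**

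From the document: 50 per arm, two-sided 5%, and 40% as a base rate. Assumed: no true effect, and a gap *s* between the arms' expected effective rates that arises only from who was let in.

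With rates 0.40 ± s/2:

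- SE under equality = √(2·0.40·0.60/50) = 0.0980; critical difference = 1.96 × 0.0980 = 0.192.
- s = 0.10: rates 0.45 and 0.35; SE = √((0.2475 + 0.2275)/50) = 0.0975; (0.192 − 0.10)/0.0975 = 0.944; upper tail 0.173, lower tail 0.001; total 0.174.
- s = 0.15: rates 0.475 and 0.325; SE = 0.0968; (0.192 − 0.15)/0.0968 = 0.434; upper tail 0.332, lower tail below 0.001; total 0.332.
- s = 0.05, the same way: 0.080.

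Exact enumeration of the uncorrected chi-squared test, with base rates from 0.40 to 0.55 in one arm and *s* added in the other, gives about 18% for 10 points and 34% for 15 points. The normal approximation above (17% and 33%) agrees.

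**The case against.** **The roles and the timing are inferred.** The article uses two titles and never equates them. It does not say who keeps the list or when an assignment becomes known. This stands. A reader might infer that the list is open, or that the recruiter does see the next assignment; the article says neither. What it supports is that concealment is not assured as described.

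**A condensed article may leave envelopes or a list holder to the full protocol.** This also stands, so their absence is not the point. The point is what the article does state: the one sentence on who knows the allocation names a role that, on the natural reading, sits inside recruitment.

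**The sentence is about assessor blinding.** That is plausible from its position, and the rule against exchange between assessors and care providers presupposes that the latter know the arm. The sentence is then loosely worded, since the therapists must know too. That looseness is no evidence of selection, but under this reading the article offers no safeguard against selection at all.

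**Simple randomization might be blamed as well.** A reader might infer that unequal arms or chance imbalance in baseline grade are part of the fault. They are not. The 50 per group is a target, and chance imbalance does not bias a randomized comparison. Stratified blocks in an unblinded single-centre trial would make assignments easier to predict, which works against concealment.

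**The false-positive rates follow from assumed shifts.** Correct. Nothing in the article indicates a 10- or 15-point shift, and the rates show sensitivity only.

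**Conclusion.** The concern holds in a conditional form. As written, the division of roles does not protect against selection at entry, and every safeguard described acts later. This rests on two readings that the text leaves open: that primary researcher and primary investigator are one role, and that the investigator's knowledge of the allocation may come before eligibility and consent are settled.

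Neither actual selection nor its size can be established from the article. The figures of about 18% and 34%, against a nominal 5%, apply only if entry shifted the expected effective rates by 10 or 15 points. The sample size is unaffected. The matter still deserves correction, because a positive result would remain open to a selection explanation that no later analysis could fully exclude. The article reports that recruitment was not complete at submission.

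**What to change.** Replace the sentence on who knows the allocation with text that states three things:

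1. The sequence is generated and held by someone with no part in recruitment, training or assessment. The hospital's Clinical Trial Office, already named in the adverse event section, is one candidate.
2. Each assignment is released only after eligibility, signed consent and the baseline speech breathing grade have been recorded.
3. The treating therapists know the arm and the outcome assessors do not.

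If the primary researcher and the primary investigator are different people, or if assignments were already released only after consent, say so. Simple randomization needs no change.

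The cost is a short amendment and one small logistical step per enrolment, with no extra patients. The change protects only patients enrolled after it, so the report should state how assignments were held before that date.

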### Treatment

The *LQG* (study group) or traditional breathing (control group) training followed by basic articulation training (20 min for each) will be conducted five times per week for 3 weeks in a soundproof, 10 m^2^ room with a background noise of ≤ 30 dBA. Training will be provided by experienced investigators who will ensure that the process is performed in accordance with the protocol. Briefly, a patient will first need to adjust to a straight sitting position, perform relaxing breathing with help from regular upper-limb movement, and be instructed to breathe in smoothly through the nose and exhale slowly through the mouth.

